### Procedures

All participants will receive individualized physiotherapy, consisting of supervised functional physiotherapy with the aim to improve daily functioning. The intervention is based on guided exercises for low back pain, psychoeducation in coping with pain and encouragement of daily exercise. No manual treatment approaches will be used. The program will be delivered in 4–8 sessions of 1–2 h. The physiotherapy will be performed by physiotherapists in the center according to the European guidelines for the management of chronic low back pain [27]. Fewer than 4 completed sessions are considered as non-compliance.

### The somatic experiencing® intervention

In the SE intervention, patients receive up to 12 sessions of 1 h SE therapy delivered by a certified SE therapists (a physiotherapist or a pain nurse) with several years of experience in SE and pain management. The SE intervention follows the nine-step model as outlined by Peter Levine [21] and involves gradually eliciting awareness of body sensations associated with the traumatic event. By the process of ‘titration’, patients are gradually encouraged to access, feelings and body sensations as means to restore equilibrium to the autonomic nervous system and thereby alleviate hyperarousal, re-experiencing and avoidance of trauma-related experiences and thoughts. Fewer than 6 sessions are considered as non-compliance.

The overall allowable time frame for the interventions is 16 weeks. The expected timeframe for the final treatment and post-intervention assessment is 12–14 weeks for the SE + physiotherapy group and 8–10 weeks for the group only receiving physiotherapy. An overview of the program is outlined in Table 1.

**Table 1 Tab1:** Overview of the SE Intervention

Steps	Theme	Therapeutic approach
1	Create a safe environment	To facilitate a therapeutic environment that promotes a feeling of security. Build a therapeutic relationship with the patient. The therapist assumes an accepting stance.
2	Support initial exploration of sensations	To support a mindful approach to the exploration of bodily sensations. Facilitate the experience of positive sensations.
3	Pendulation	By the process of “pendulation” to encourage the patient to come in contact with bodily sensations. To help the client experience how the body alternates between pleasant and unpleasant sensations. By facilitating this awareness, the patient learns how to relax.
4	Restore active defensive responses	To help the patient to restore active defensive responses that has “collapsed” because of the overwhelming nature of the trauma. Support impulses to active responses, including defensive orienting, fight and flight.
5	Titration	Because the central nervous system cannot distinguish between the original trauma and being overwhelmed by the re-experience of the traumatic event in therapy, the aim is to help the patient to gradually move in and out of the trauma. This by ensuring a continuous grounding in the body with attention to the bodily responses while moving into and out of the content of the traumatic event.
6	Uncoupling fear from immobility	Traumatic events activate a flight-fight response. When the traumatic event remains unresolved, the body collapse and becomes “frozen”. The aim is to help the patient to experience this response of immobility in a safe environment and enable immobility to dissolve.
7	Encouraging the discharge of energy	To help the patient to discharge accumulated energy during the traumatic event. Help the client to experience and resolve hyper-arousal states in a safe environment.
8	Restore equilibrium through self-regulation	Through cyclical discharges of energy to help the patient to “reset” the nervous system and feel more empowered to regulate themselves. Allowing time for integration and reverberation.
9	Restoration to the here-and-now	Gently invite the patient to return to the outer world after being attentive to inner sensations and experiences.

*Note.* The nine steps are building blocks and not linear steps. The nine steps are intertwined and may be accessed repeatedly. Adapted from (Levine [21], chapter 5)

### Outcome measures

All outcomes are obtained by an investigator blinded to group allocation at baseline, post-intervention, and at follow-up at 6 and 12 months post-randomization. The outcomes are as follows:

### Primary outcome

The primary outcome is disability 6 months post-randomization measured with the modified version of the Roland Morris Disability Questionnaire (RMDQ-23; [28]). The RMDQ-23 is a self-reported outcome measuring the level of disability related to low back pain. The level of disability is measured on 23 statements covering six different domains: physical ability/activity, sleep/rest, psychosocial level of functioning, household management, eating, and pain frequency. Each statement is scored 1 if the patient feels that the statement is descriptive of their circumstances and scored 0 if not. The total RMDQ score ranges from 0 (no disability) to 23 (maximal disability). Scores are converted to percentages with 23 corresponding to 100% disability. The trial is powered to detect a 20% reduction on the RMDQ from baseline to 6 months follow-up (post randomization). Both internal consistency (Cronbach’s alphaα = 0.84 to 0.96) and test-retest reliability (*r* = 0.83 to 0.91) of the RMDQ are good [29].

### Secondary outcomes

PTSD symptoms are measured using the Harvard Trauma Questionnaire part IV [26]. The Harvard Trauma Questionnaire consists of 17 items with a 4-point Likert scale (1 = not at all to 4 = very often). The 17 items relate to PTSD’s core clusters: avoidance (7 items), re-experiencing (5 items), and hyperarousal (5 items). An item is deemed to be positively endorsed if scores are ≥3. The Harvard Trauma Questionnaire follows the diagnostic criteria for the PTSD diagnosis according to the DSM-IV. In the current study, a possible PTSD diagnosis is proposed if participants report at least one re-experiencing symptom, three avoidance symptoms, and two hyperarousal symptoms. Possible sub-clinical PTSD is proposed in cases where the patients either miss one symptom of avoidance or hyperarousal. The Harvard Trauma Questionnaire self-report measure of PTSD has previously been reported as having an 88% concordance with interview-based estimates of PTSD [26].

Pain intensity is measured as the average score of three 11-point Likert scales measuring peak pain intensity, average pain intensity over the past 2 weeks as well as current pain intensity [30]. Each scale measures pain intensity on a 0–10 numerical rating scale (NRS: [31]) with 0 defined as no pain and 10 as the worst imaginable pain.

The Pain Catastrophizing Scale [32] is used to measure catastrophic thinking related to pain. The PCS ask participants to reflect on past painful experiences, and to indicate the degree to which they experienced each of 13 thoughts or feelings when experiencing pain, on a 5-point Likert scale with (0 = not at all, 4 = all the time). A scale sum score is calculated from all items, with a high score indicating a high level of pain catastrophizing.

Fear of re-injury due to movement is measured with the Tampa Scale for Kinesiophobia (TSK: [33]). TSK is a 17-item scale assessing fear of movement on a 4-point Likert scale ranging from 17 to 68 with higher scores indicating higher levels of kinesiophobia. The scale is commonly used in diverse chronic pain samples and has good construct and predictive validity [34, 35].

To assess the level of depressive symptoms, we used the depression subscale of the Hospital Anxiety and Depression Scale [36]. The HADS was originally constructed to detect anxiety and depression in non-psychiatric medical patients. It was later shown to be useful as a “case finder” also in other populations and it is a well-validated questionnaire with good psychometric properties [36]. The depression scale consists of 7 items related to depression (HADS-D) with responses ranging from 0 (no symptoms) to 3 (maximum impairment).

### Statistics

The sample size of 140 patients was calculated a priori. This sample size provided 80% power to detect a 20% difference in disability on the RMDQ from baseline to 6 months follow-up. This calculation assumed an α of 0.05 and allowed for up to 10% loss to follow up and non-compliance.

The primary and secondary outcomes measured at baseline, post-intervention, 6 and 12 months follow-up (post randomization) will be analyzed using linear mixed-effects models (random coefficient models and multilevel models). With the mixed effects model all data will be used and intention-to-treat analyses applied. Additionally, per-protocol analyses will be applied. Gender and age will be entered as covariates in all models. Assumptions of linearity, homogeneity of variance and normality will be tested.

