### Randomization and masking

Patients are randomized by random permuted blocks of six. Randomizations are consecutively numbered in sealed opaque envelopes and administered by a project nurse, blinded to treatment assignments. Patients are randomly allocated to one of the two conditions: Somatic Experiencing® (SE) + physiotherapy (PT) or PT alone. Treatment is initiated within 2 weeks after randomization. Measurements of effect are carried out at baseline before randomization, post-intervention, 6 and 12 months post-randomization. The study statistician will be blinded to treatment allocation.

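### The covariates named are gender and age only, and the plan neither adjusts for baseline RMDQ nor says the arms share a baseline mean, so the 6-month comparison may be less precise than the collected data allow

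*Protocol article*

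**What the plan says.** The Statistics section of the protocol article plans linear mixed-effects models, described as random coefficient and multilevel models. The measurements modelled as outcomes are baseline, post-intervention, 6 months and 12 months. On covariates it says: "Gender and age will be entered as covariates in all models". It does not list the baseline value of the outcome as a covariate. It also does not say whether the arms have a common baseline mean, how time is coded, or which model term is the primary comparison.

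The Randomization and masking section fixes the timing: "Measurements of effect are carried out at baseline before randomization, post-intervention, 6 and 12 months post-randomization". It describes permuted blocks of six and names no stratification factor.

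The power statement is worded as change: "This sample size provided 80% power to detect a 20% difference in disability on the RMDQ from baseline to 6 months follow-up". The Primary outcome section describes the powered effect in the same way, although it defines the outcome itself as disability at 6 months.

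**The concern.** The pre-randomization value of an outcome is usually among its best predictors. The article publishes a covariate set for all models and leaves that value out. Baseline therefore enters only as a response, and what that achieves depends on a detail the article does not give.

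If each arm has its own baseline mean, two 6-month contrasts are available. The difference in 6-month level makes no use of baseline. The difference in change from baseline subtracts the whole baseline difference, which over-corrects whenever r is below 1. A baseline-adjusted analysis is more precise than either for any r strictly between 0 and 1.

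The choice also decides how a chance baseline difference reaches the result, since no stratification on baseline disability is described. The stake is a wider confidence interval, and lower power than the same data could give, on an outcome planned at 80% power. The Background reports that the earlier trial of this therapy found no added effect on disability.

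**Working it through.** **Inputs from the documents.** 140 patients, 70 per arm; power 80%; and "This calculation assumed an α of 0.05 and allowed for up to 10% loss to follow up and non-compliance". Sidedness is not stated, and two-sided is assumed.

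**Inputs not in the documents.** No SD, baseline mean or baseline-to-6-month correlation r is given. I take r = 0.4 to 0.7 as an assumption. The article's "test-retest reliability (*r* = 0.83 to 0.91) of the RMDQ are good" concerns repeat measurement, not correlation over 6 months of treatment. It is used only to note that the assumed range lies below it.

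**Step 1: the plan's own figure.** The 140 cannot be derived without an SD, but it can be solved backwards. With standardised difference d, n per arm = 2(1.960 + 0.842)²/d². At d = 0.50 this is 2 × 7.85/0.25 = 62.8, so 63 per arm. Then 63/0.9 = 70 per arm, or 140 in total. So 140 is consistent with d = 0.50, though the article states no d and does not say which SD would apply. (The t-test version gives 144.)

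**Step 2: variance factors.** Take categorical time, complete data and equal variances at baseline and 6 months. Relative to the variance of the raw 6-month difference:
- 6-month level, baseline means free: 1
- change from baseline, baseline means free: 2(1 − r)
- baseline as covariate, or baseline means constrained equal: 1 − r²

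Adjusted against change: (1 − r²)/[2(1 − r)] = (1 + r)/2. Adjusted against level: 1 − r². A generalised least squares calculation with four visits and compound symmetry gave the same factors. At r = 0.5 they were 1.00 for change, 1.00 for level and 0.75 for the constrained model. At r = 0.7 they were 0.60, 1.00 and 0.51.

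**Step 3: gain over the change contrast.** The standard-error ratio is √[(1 + r)/2]. Power at 63 per arm is Φ(0.5 × √(63/2)/√f − 1.96), where f is the variance factor. In the power column d = 0.50 is placed on the change-score SD, so that the unadjusted change contrast (f = 1) has 80.1% and the adjusted analysis has f = (1 + r)/2.

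| r | variance ratio (1 + r)/2 | variance cut | SE cut | adjusted power |
|---|---|---|---|---|
| 0.4 | 0.70 | 30% | 16.3% | 91.8% |
| 0.5 | 0.75 | 25% | 13.4% | 90.0% |
| 0.6 | 0.80 | 20% | 10.6% | 88.1% |
| 0.7 | 0.85 | 15% | 7.8% | 86.1% |

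If d = 0.50 is placed on the raw-score SD instead, power goes from 72.6% to 86.5% at r = 0.4, from 80.1% to 90.0% at r = 0.5, and from 95.2% to 97.6% at r = 0.7.

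**Step 4: gain over the raw 6-month difference.** The variance cut is r²: 16% at r = 0.4, 25% at 0.5, 36% at 0.6 and 49% at 0.7.

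**Step 5: chance imbalance.** Suppose the arms differ at baseline by D through chance. Given D, the level contrast is shifted by rD and the change contrast by −(1 − r)D. For r = 0.4 to 0.7 that is 0.4D to 0.7D, or −0.6D to −0.3D. The adjusted contrast is not shifted.

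**The case against.** The strongest objection is that the article never says the baseline means are free. A constrained longitudinal model also keeps baseline as a response with gender and age as covariates, so the published text is compatible with the model recommended here. Parametrisation is often left to an analysis plan, which is not shown. This stands: a reader might infer that the trial has committed to an unconstrained baseline, and the text does not support that. The loss in the working is therefore conditional. What remains is that the article did publish a covariate set for all models, omitted baseline from it, and as written allows either less precise contrast.

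A reader might also take the raw 6-month difference as the planned comparison and quote a power gain from 80% to between 86% and 98%. The power wording points to change from baseline, and against that the gain is smaller at the upper end of the range and shrinks as r rises. The raw difference is the less likely reading, although the Primary outcome section's definition of the outcome does not exclude it.

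It is also fair to say that a change contrast already uses baseline, that d and r are not in the documents, and that the formulas assume categorical time and complete data. A random coefficient model with continuous time would borrow across visits and give a different contrast. These points limit the size of the gain. Under categorical time they do not change its direction.

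**Conclusion.** The point holds as a matter of precision and of protection against chance imbalance. Gender and age are the only covariates named, baseline is placed among the outcomes with no stated constraint, and the 6-month contrast is not named.

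If the baseline means are free and the contrast is change from baseline, adjustment would lower the variance by 30% to 15% for r from 0.4 to 0.7. If the 80% refers to the change score, power would become about 90% at r = 0.5 and 86% at r = 0.7. These figures rest on an assumed r, on d = 0.50 solved backwards from the 140, on 63 evaluable patients per arm, on categorical time and on complete data.

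Two stronger conclusions are not supported. Neither unadjusted contrast is biased under randomization. Nor is the sample size of 140 shown to be wrong, since adjustment would only add to the planned power.

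**What to change.** In the Statistics section, state that the primary comparison is the between-arm difference in RMDQ at 6 months, from a repeated-measures model with categorical time and baseline means constrained equal across arms. Alternatively, remove baseline from the response and enter it as a covariate. Use one form or the other, not both. Keep age and gender. Apply the same rule to each secondary outcome with its own baseline value.

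The constrained form keeps every baseline measurement in the model, which fits the article's intention to use all data. The cost is a sentence or two of text, with no new data and no change in sample size. It should be settled before outcomes are compared by arm.

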## Discussion

The primary aim of the present study is to investigate the potential additional effect of a SE intervention in addition to physiotherapy (PT) compared to PT alone for patients with chronic low back pain and comorbid PTSD. The intervention is expected to have an additional positive effect on both disability and all secondary outcomes compared to PT alone. Also, as indicated by earlier preliminary results in whiplash, the comorbid presence of PTSD seems to prevent a good response to physiotherapy [14]. For these reasons, it is believed that an effective treatment of PTSD combined with supervised exercises for low back pain will have an additional effect on both disability and pain. Although Andersen and colleagues [15] only found SE to have a significant effect on PTSD symptoms and fear of movement (kinesiophobia), a number of limitations by the study makes it impossible to draw definite conclusions about the possible additional effect of SE on disability and pain. First of all, the SE intervention was very brief and the trauma symptoms were severely chronic dating back decades. Also, a more structured physiotherapeutic program needs to be tested in combination with a full-length SE program.

The study addresses a prevalent problem, chronic low back pain. Comorbid PTSD is currently not targeted in back pain rehabilitation although highly prevalent after back pain related to injuries. If the SE intervention shows to have an additional effect in disability and pain, the study is likely to have a positive impact on the management of chronic low back pain and will have immediate clinical applicability.

## Abbreviations

CBT: Cognitive Behavioral Therapy
HADS: Hospital Anxiety and Depression Scale
LBP: Low Back Pain
MRI: Magnetic Resonance Imaging
MVC: Motor Vehicle Collision
NRS: Numerical Rating Scale
PCS: Pain Catastrophizing
PT: Physiotherapy
PTSD: Post Traumatic Stress Disorder
RCT: Randomized Controlled Trial
RMDQ: Roland Morris Disability Questionnaire
SE: Somatic Experiencing®
TAU: Treatment As Ususal
TSK: Tampa Scale for Kinesiophobia
